###### Subgroups analysis

Seven subgroups analysis will be performed, including subgroup by age, subgroup by gender, subgroup by weight, subgroup by BMI, subgroup by platelet function, subgroup by ischemic lesion, and subgroup by the type of surgery. Subgroup analyses are limited to the primary efficacy endpoint and safety endpoint only. Separate Cox models will be applied to each subgroup during subgroup analysis.

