### Procedure and data collection

Data collection includes demographic information, clinical information, imaging information, and laboratory examinations. The details are shown in Table 2.

**Table 2 tab2:** Information collection.

Information collection	Content
Clinical information	Demographic information, health economics information, physical examination, etc.
Surgery information	Type of surgical treatment, blood information, hemostasis subjective difficulty score, etc.
Clinical score	mRS score, GCS, ICH score, GOS
Special examinations of MACCPE	Head CT, venous ultrasound of lower extremities, myocardial enzyme, thromboelastogram
Others laboratory examinations	Blood routine, biochemistry, coagulation function
Outpatient or phone review	Rebleeding event, MACCPE, survival condition

The procedure includes screening (Step 1), randomization and administration (Step 2), and outcome evaluation (Step 3; Figure 1; Table 3).

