### Monitoring the effectiveness of antiplatelet therapy

Before and after aspirin administration, we will assess the platelet function. The platelet function will be assessed using the thromboelastogram (TEG). All parameters, including maximum amplitude (MA), citric acid kaolin (CK), reptilase (A), aspirin (AA), are recorded through standard tracing. Based on MA, the rate of platelet function inhibited by aspirin (AA%) was calculated using the formula as shown below:

$$AA\%=\frac{MA\left(CK\right)-MA\left(AA\right)}{MA\left(CK\right)-MA\left(A\right)}$$

For patients in the early start group, the platelet function will be detected before aspirin administration and 7 days after administration. AA% > 50 is defined as the good response to aspirin. Moreover, for the patients in the normal start group, because they do not receive any antiplatelet therapy, the platelet function assessment do not need to perform for these patients.

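### The sections on platelet-function testing conflict over whether controls are tested, which leaves that subgroup's basis unsettled; separate Cox models per subgroup do not test whether the treatment effect differs

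*Protocol article*

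**What the plan says.** Under Subgroups analysis, the protocol article lists seven factors: age, gender, weight and BMI, then "subgroup by platelet function, subgroup by ischemic lesion, and subgroup by the type of surgery". It adds that "Subgroup analyses are limited to the primary efficacy endpoint and safety endpoint only" and gives the method: "Separate Cox models will be applied to each subgroup during subgroup analysis". No interaction term is named.

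Under Monitoring the effectiveness of antiplatelet therapy, it says: "For patients in the early start group, the platelet function will be detected before aspirin administration and 7 days after administration". The only category defined there is an aspirin inhibition rate (AA%) above 50, labelled a good response to aspirin. For the normal-start arm, on the ground that these patients receive no antiplatelet therapy, "the platelet function assessment do not need to perform for these patients".

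Table 2, under Procedure and data collection, lists the special examinations of MACCPE as "Head CT, venous ultrasound of lower extremities, myocardial enzyme, thromboelastogram". Table 3 schedules the special examinations within 72 h, at 10 ± 4 days and at 90 days, without separating the arms. It places randomisation at 3 days.

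**The concern.** A treatment effect within a platelet-function stratum needs patients from both arms in that stratum, classified by something that treatment cannot have changed. The monitoring section appears to remove the control patients. The one category it defines is a response to the assigned drug.

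The modelling sentence raises a second issue, and it applies to all seven factors. A subgroup analysis is meant to show whether the effect of early aspirin varies between kinds of patient. Fitting each stratum separately does not answer that. With few events, one stratum can easily reach p < 0.05 while the other does not, even when the true effects are equal. Because re-hemorrhage is one of the two endpoints analysed, a mistaken subgroup claim could concern safety as well as efficacy.

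**Working it through.** **1. Is platelet function available in both arms before randomisation?**

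| Place in the protocol article | Early-start arm | Normal-start arm |
|---|---|---|
| Monitoring the effectiveness of antiplatelet therapy | before aspirin and 7 days after | need not be done |
| Tables 2 and 3 | within 72 h, 10 ± 4 days, 90 days | same, no split by arm |

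- If the monitoring section governs, controls have no value, every stratum contains early-start patients only, and a within-stratum hazard ratio cannot be estimated.
- If the tables govern, both arms have a value from before randomisation at 3 days, and a valid baseline subgroup can be formed.

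The article does not say which applies.

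**2. Could 7-day AA% be the factor?** It is measured after randomisation and on aspirin. Controls have no counterpart, so responders would be set against unselected controls. Aspirin starts at day 3, so the value arrives at about postoperative day 3 + 7 = 10. The Discussion puts the MACCPE peak at the seventh day after surgery, so some patients would have their event before they could be classified. It is unsuitable whichever section governs.

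**3. What separate models can show.** The plan gives no figure for its subgroup analyses, so there is none to reproduce. The illustration below takes its inputs from Sample size: 125 patients per arm, a 10.8% control rate and a reduction of 5%, read here as 5 percentage points (to 5.8%). Two equal strata per factor are my assumption.

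- Events: 125 × (0.108 + 0.058) = 20.75, or 10.375 per stratum.
- Implied hazard ratio: ln(1 − 0.058) / ln(1 − 0.108) = 0.523, with log −0.649.
- Power of one stratum's Cox model, two-sided 5%: Φ(√(10.375/4) × 0.649 − 1.96) = Φ(−0.915) = 18%.
- Chance that exactly one of two strata is significant when both share this hazard ratio: 2 × 0.18 × 0.82 ≈ 30%.

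**4. What an interaction test can show.**

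- Standard error of the difference in log hazard ratios: √(4/10.375 + 4/10.375) = 0.878.
- Power for a ratio of hazard ratios R: Φ(ln R / 0.878 − 1.96). This gives 12% for R = 2, 24% for R = 3 and 35% for R = 4.
- R needed for 80% power: exp((1.96 + 0.842) × 0.878) ≈ 11.7.

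**5. Range for the event count.** The 10.8% is for cardiovascular and cerebrovascular events, while MACCPE also counts pulmonary embolism and deep venous thrombosis. The Introduction also says the rate may be higher in high-risk patients.

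| Total events | SE, √(8 / events per stratum) | Power at R = 2 | Exactly one stratum significant at common HR 0.523 |
|---|---|---|---|
| 20.75 | 0.878 | 12% | 30% |
| 41.5 (doubled) | 0.621 | 20% | 43% |
| 75 | 0.462 | 32% | 50% |

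The last row is the count needed for 80% power overall: 4 × (1.96 + 0.842)² / 0.649² ≈ 75. More events help the interaction test but do not remove discordance between strata.

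**6. Multiplicity, illustrative only.** With no effect anywhere and independent tests, 7 factors × 2 endpoints = 14 tests give 1 − 0.95¹⁴ = 51%. With two levels per factor, 28 tests give 1 − 0.95²⁸ = 76%.

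**The case against.** The best defence of the subgroup is that the monitoring section concerns response to aspirin. Its reason for exempting controls, that they take no antiplatelet drug, fits on-treatment monitoring better than screening. On that view Tables 2 and 3 supply a baseline value for everyone. This is a fair reading, so a flat statement that the subgroup cannot be analysed would go too far. The conflict remains, because the same section also covers the pre-aspirin test and then exempts controls from the assessment without qualification.

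A reader might also infer that 7-day AA% is meant to define the subgroup. The article does not say so. The objection to that measure is a warning against one possible choice.

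On the models, stratum hazard ratios are ordinary subgroup output, and an article may leave interaction tests to a fuller plan. A reader might infer that effect modification will be declared when one stratum is significant and the other is not, but no such rule is stated. What stands is that the article fixes a method, and that method alone cannot show a difference in effect.

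Finally, the interaction test has little power. That is true, and it is a reason to label the results exploratory. It does not make separate models more informative.

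**Conclusion.** The point holds in two parts. First, the sections on platelet-function testing contradict each other and must be reconciled. The subgroup comparison is not estimable if the control-arm exemption governs, and it can be estimated from a baseline value if the tables were followed. Second, the stated modelling method does not test whether the effect differs between subgroups.

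On the article's rates, with two equal strata, a shared hazard ratio of 0.523 would leave exactly one stratum significant about 30% of the time. An interaction test would have about 12% power for a two-fold ratio of hazard ratios. Both figures rest on about 21 events, a count drawn from a narrower endpoint than MACCPE.

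The 51% and 76% should not be read as the trial's actual false-positive risk. The article states no number of levels per factor, and the tests are not independent: weight and BMI are related, and every factor re-divides the same patients. The conclusion does not depend on these figures. The primary efficacy and safety comparisons are untouched.

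**What to change.** 1. Reconcile the monitoring section with Tables 2 and 3, stating whether normal-start patients have a thromboelastogram before randomisation.
2. If both arms have one, define the platelet-function subgroup from that value only. If not, drop the subgroup.
3. Keep 7-day AA% as a descriptive measure within the early-start arm.
4. Replace the separate models by one Cox model per subgroup factor and endpoint, with treatment, the factor and their interaction. Report stratum hazard ratios with 95% confidence intervals and the interaction p-value, labelled exploratory.

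Items 3 and 4 need only a change of wording. Items 1 and 2 depend on what was done at the sites. Recruitment began in May 2021 and the article appeared in November 2022, so baseline values not taken from controls cannot be recovered, and the platelet-function subgroup may be lost. The remaining price is low interaction power, which should be stated with the results.

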#### Data management

The clinical research coordinator (CRC) will make regular visits to each participating center to ensure the strict performance of the research program. In case of any contradiction to the study protocol, the CRC will promptly report this to the investigators. In addition, throughout this study, a summary meeting will be held every 3 months to discuss and solve any problem arising from the research or encountered by the patients.

All data will be collected and stored using case report form (CRF), and the completed CRFs will be sent back to Beijing Tiantan Hospital per 3 months. In addition, the data will be also transcribed into an electronic version by nine investigators independently. After completion, the CRFs will be sealed in a research-specific cabinet, and a particular person shall keep the electronic data. The principal investigator’s institution established a data management committee in Beijing Tiantan Hospital to monitor data quality and ensure data security. Data was accessible only to the members of the research team. The privacy of the patients involved was protected.

#### Ethical considerations

This study was granted approval from the Institutional Review Board of Beijing Tiantan Hospital (KY 2021–053-02), and the research would be conducted in strict accordance with the declaration of Helsinki and Human Biomedical Research Ethical Issues. All enrolled subjects will be informed with a complete and comprehensive introduction, including the purpose, procedure, potential risks, and potential benefits of the study. The patient’s family should sign the written informed consent before beginning. They will be informed that they have the right to withdraw from the study at any time, and informed consent will be retained as a clinical study document for future reference. The subject’s personal privacy and data confidentiality will be protected during the study.

## Discussion

E-start study is the first clinical trial of postoperative early start antiplatelet therapy in sSICH patients with high risk of ischemic events. In this study, we investigate whether early start antiplatelet therapy after surgery can prevent the incident of MACCPE, with no increasing risk of postoperative intracranial rehemorrahge.

Early start antiplatelet therapy postoperatively may reduce the incidence of MACCPE that seriously affects the clinical outcome of sSICH patients (Ding et al., 2018). However, there is no standardized protocol for postoperative antiplatelet management. Therefore, we analyzed the characteristics of postoperative MACCPE incidence by the SAP-ICH cohort (ChiCTR1900024406). We find that MACCPE occurs four postoperative days later, and the peak is the seventh day after surgery. Remarkably, there were often more than 30 days before starting antiplatelet therapy postoperatively in past research (Flynn et al., 2010; Murthy et al., 2019; RESTART Collaboration, 2019). Therefore, it may be missing the time window of the high incidence of MACCPE, which may mask treatment effects. Summarily, early start antiplatelet therapy (start in postoperative 4 days) is crucial for decease the incidence of MACCPE.

Notably, safety is another consideration in this study. The data of SAP-ICH showed that intracerebral hemorrhage events often occur 3 days following the procedure. In addition, many studies have reported the results that restarting antiplatelet therapy after ICH does not increase the risk of recurrent intracerebral hemorrhage (Flynn et al., 2010; Teo et al., 2017; Chen et al., 2018; Murthy et al., 2019; RESTART Collaboration, 2019; Diep and Garcia, 2020; Al-Shahi Salman et al., 2021). The results of an observational study published in *stroke* showed that the rate of recurrent bleeding after discharge in sSICH patients treated with antiplatelet agents was roughly the same as that in patients not treated with antiplatelet agents (Flynn et al., 2010). The “RESTART” research, a randomized controlled study published in the Lancet, further confirmed that the risk of a recurrent intracerebral hemorrhage after SICH using antiplatelet therapy is small (RESTART Collaboration, 2019). However, this assumption should be verified by the result of this study.

## Conclusion

In summary, we have described the first clinical trial for early start antiplatelet therapy for operated sSICH patients with a high risk of MACCPE. The efficacy and safety of early start antiplatelet therapy will be discussed in this study, which will provide evidences for postoperative antithrombotic management in the future.

## Ethics statement

The studies involving human participants were reviewed and approved by IRB of Beijing Tiantan Hospital, Capital Medical University. The patients/participants provided their written informed consent to participate in this study.

